#### Intervention phase

The findings of the research phase will guide the development of the multi-level intervention targeting the policy makers, officials of the Ministries of Education, Health, Youths and Sports, School Heads and Physical and Health Education Teachers and the students. A *multilevel intervention is defined as an intervention* that addresses at least three levels of the multilayer system. It target at least three sources of influence that may ultimately result in improved health behaviour and outcomes [25]. Suggested activities which were identified based on literature [24, 48, 49] are outlined in Table 3.

**Table 3 Tab3:** A list of multi-level Interventions based on a review of literature

Level	Possible Activities/Interventions
Individual Level	• Educational materials for students • Special Dance events in schools • Debates and other co-curricula activities • Experience sharing by role models/athletes • M health –SMS • Peer Education
Socio Cultural level	• Dialogue and dissemination meetings with Parent Teachers Association, Teachers, Principals
Built Environment	• Provision/Refurbishment of PA facilities
Policy/Institutional Level	• Development of curriculum &Training of Teachers • Review of PE Curriculum • Creating and training a school-based action team or small groups or committees. • Dissemination Meetings, • Production of evidence based dissemination materials – policy briefs, fact sheets etc. • One – on -one Advocacy visits • Celebration of special days and events

During baseline assessment, the students will be asked to rank a list of preferred activities which can be implemented in the school settings to improve physical activity. Activities which are under consideration include educational materials for students, special dance events in schools, debates and other co-curricula activities, experience sharing by role models/athletes, Mhealth and peer education. The preferred interventions will be jointly developed by the adolescents, school authorities and the researchers. At the school level, activities under consideration include meetings and policy dialogue forums, production of evidence based dissemination materials on the importance of physical activity for the health and mental well being of students, and advocacy visits to engage policymakers to prioritise resources aimed at promoting physical activity in schools. The policy goal for this intervention is to ensure that all in-school adolescents participate in 30 minutes of daily structured moderate to vigorous physical activity. Meetings will be held with Physical and Health Education Teachers to translate this policy objective into concrete activities and a work plan which will guide the intervention will be jointly developed. Issues which will be discussed at the meetings with the policy makers, physical health education teachers and principals include the perceived health implication of physical inactivity, risks of overweight and obesity among young people, ways to promote physical activity using existing infrastructure, allocation of 50% of physical education classes for activities. At the school level, a coordination committee will be set up to facilitate the implementation of the activities. The intervention phase will span three months and a post-intervention evaluation will be conducted to assess the outcome of this intervention.

The intervention will be implemented school wide however, the baseline and post-intervention measurements will only be conducted with the selected respondents enrolled as the cohort or index children at the commencement of the study.

### Monitoring of intervention

The intervention activities will be monitored through meetings with the school heads and Physical and Health Education Teachers to ascertain the extent of implementation of the activities.

### Validity

To ensure the validity of the tools, several steps will be taken. The tools will be adapted using simple English Language and if necessary, it will be translated into Yoruba Language to suit the Nigerian context. The tools will be reviewed for content and construct validity by specialists in physical activity and school health and pretested among similar respondents in selected schools in another LGA not used for the study.

### Reliability

To ascertain the reliability of the instrument, analysis of pre-test data will be done using Cronbach’s Alpha correlation coefficient of the IBM Statistical Package for Social Sciences (SPSS). A correlation coefficient greater than 0.7 will imply that the tool is reliable.

In order to ensure accurate and consistent measurements, the weighting scale will be calibrated with a known weight and the height scale will be checked and recalibrated daily before measurements commence.

Research assistants will be recruited and trained to assist in data collection and provision of support to students in completing the recall sections of the tools. Training sessions will include objectives of the study, importance of collecting accurate data and ethical issues. The questionnaire will be reviewed with them to ensure common understanding. They will be trained to relate skillfully and courteously with the respondents. At the end of the training session, the research assistants will role-play the administration of the questionnaires to demonstrate an understanding of the intricacies involved in data collection.

#### Data management and statistical analysis

Serial numbers will be assigned to the questionnaires for easy identification and recall of the instrument and these will be stored in a place safe. A coding guide will be developed and sections of the tools which are open ended will be coded before data entry. The data will be cleaned to identify and correct all errors. The quantitative data will be analyzed using STATA version 13.

There are two key primary outcome variables specifically step count measured with pedometers which is a continuous outcome variable and self-reported physical activity level which can be a continuos or ordered categorical variable, details in Table 4.

**Table 4 Tab4:** Description of outcome Measures

	Description of outcome measures	Type of Variable
Primary Outcome Measures	Self-reported physical activity score/levels	Continuous
		Ordered categorical
	Step count (average steps/day)	Continuous
Secondary Outcome Measures	Anthropometric Measurements (measured using body mass index)	Ordered categorical
	Fitness level measured using the 20-mSRT	Ordered categorical
	Knowledge of the health benefits of physical activity	Ordered categorical
	Attitude toward Physical activity	Ordered categorical
	Self efficacy	Ordered categorical
	Perceived behavioural control and intention	Ordered categorical
	Social Norms and Social support,	Ordered categorical
	Policy or programme changes	Qualitative

At baseline, bivariate analysis (cross tabulation) will be used to compare the differences in proportions of the primary and secondary outcome measures of the experimental and control groups. Chi-square test (X^2^) will be used for significance testing of the self-reported physical activity levels (dependent ordered categorical variable) and other categorical independent variables while repeated measures ANOVA will be used for Step count (average steps/day). Based on data generated using bivariate analysis, all independent variables which are significant at 10% will be incorporated into the regression model.

Regression analysis will be used to assess the extent to which the independent variables predict self-reported physical activity levels and step count (average steps/day). Level of significance will be 5% at 95% confidence interval. The effect of the intervention will be tested using multilevel mixed effects models for repeated measures adjusted for relevant confounding factors. This approach ensures that the longitudinal and hierarchical structure of the data are considered in the analysis. Because of the clustered structure of the data, random effects for the cities and schools will be included in all analyses.

The qualitative data will be transcribed, coded, entered into NVIVO version 10 and analyzed using thematic approach. Points of agreement and disagreement among discussants with reference to the study objectives will be noted.

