### Sample size for the intervention study

The minimum sample size for this study was obtained using the formula for calculating sample size for two proportions with the aim of detecting a difference in outcomes between the groups [23]. The effect size of a similar study which was conducted in Denmark [24] and the prevalence of moderate and high intensity physical activity reported by Odunaiya et al., 2010 [12] were used for calculating the minimum sample size. A multi-level intervention to promote physical activity among in-school adolescents has not been conducted in Nigeria and the effect size is unknown. This justifies the use of the value reported in Denmark [24]. A *multilevel intervention is defined as an intervention* that addresses at least three levels of the multilayer system. It target at least three sources of influence that may ultimately result in improved health behaviour and outcomes [25].

Intracluster correlation coefficient (ICC) is a measurement that captures between-cluster and within-cluster variability in outcome and is required for sample size calculation in clustered studies that comprise exposed or unexposed clusters [26–29]. To account for this, the intracluster class correlation reported by Oyeyemi et al., (2014) which assessed participants’ self-reported active transportation to school and leisure-time Moderate-to-Vigorous Physical Activity (MVPA) among in-school adolescents was used to estimate the within and between school variation in physical activity in order to control for clustering within the schools (ICC = 0.38) [30]. The formula is outlined below:$$ \mathrm{n}=\frac{{\left({Z}_{\alpha /2+}{Z}_{\beta}\right)}^2\left[{\mathrm{P}}_1\left(\ 1-{\mathrm{P}}_1\right)+{\mathrm{P}}_2\left(\ 1-{\mathrm{P}}_2\right)\right]}{{\left({\mathrm{P}}_{1\hbox{--} }{\mathrm{P}}_2\right)}^2}\times \left[1+\left({\mathrm{m}}_{\mathrm{o}}-1\right)\times \mathrm{ICC}\right]. $$where Z_α/2_ is the critical value of the normal distribution at α/2 (e.g. for a confidence level of 95%, α is 0.05 and the critical value is 1.96), Z_β_ is the critical value of the normal distribution at β (e.g. for a power of 80%, β is 0.2 and the critical value is 0.84) and P_1_ and P_2_ are the expected sample proportions of the two groups.

Z_α/2_ = 1.96 at 5% level of error.

Z_β_ = 0.84

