P_1_ = 62% i.e. the proportion of the participants in the unexposed (control) group who are either moderately or vigorously physically active *(58.8% engaged in moderate physical activity levels while 3.2% engaged in high physical activity levels based on the study by Odunaiya, et al., 2010)* [12].

P_2_ = 72% i.e. the proportion of the participants in the exposed (experimental) group who are expected to become physically active 12 weeks after the intervention. This translates to the effect size i.e. 10% increase in the outcome measure of physical activity at follow up [24].

*ρ* = 0.38 [30].

The design effect or variance inflator factor = [1+ (k-1) x*ρ*

k = approximately the average number of individuals to be sampled per cluster. This will be 50 per school.

Three hundred and thirty six per group is the minimum sample size needed to detect whether the stated difference exists between the two proportions. A total of one thousand in-school adolescents will be selected for the study (500 for the control and 500 for the experimental group) to account for loss to attrition and increase the precision for the point estimate for physical activity behaviours among the adolescents.

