### Data collection

The data collection will be at three time points the first will be at baseline (T0), the second will be immediately after the 12-week intervention (T1) while the third will be three months after the intervention (T2). Details in Table 1. The data collection will employ a mixed methods approach including:(i)A desk review of relevant state and national NCDs prevention policies and guidelines on physical activity and an assessment of the level of coherence of the School Health Promotion policy with these policies. Other documents which will be reviewed include the Physical Health Education curriculum and school timetable to assess the opportunities for PA during school hours. The policies which regulate the construction of schools will also be reviewed to assess the extent to which these documents regulates or influences the built environment and physical activity levels in school.(ii)Physical and Health Education Teachers will complete the School Physical Activity Policy Assessment tool (S-PAPA) – a standardised semi-structured tool which assesses physical education, recess and other physical activity opportunities before, during and after school [31]. For this study, only two components will be assessed - physical education and recess. Scores on the S-PAPA tool will be tabulated based on policies and practices identified as being related to children’s physical activity during school [32, 33]. Total point scores will also be either median-split into high- and low or stratified by percentile for analysis [34].(iii) Focus Group Discussions and In-depth interviews will be held with teachers and school principals respectively to assess their opinion about social norms and support and the extent of implementation of physical activity policies and programmes in schools, level of funding, and the frequency of engagement in structured physical activity. Observations will be conducted to document facilities for physical activity in the schools using the Sport, Physical Activity and Eating behaviour: Environmental Determinants in Young people (SPEEDY) checklist. The SPEEDY checklist measures the built environment of schools and can be scored to quantify environmental support for physical activity [35]. The checklist assesses school-level environmental variables such as *Walking Provision, Cycling Provision, Aesthetics, Sport and facility provision, Other facility and Design of the school grounds* [36] The scores from each of the key variables will be dichotomised into low and high based on percentiles, and the school physical activity suitability index will be computed [36, 37].(iv) A cross sectional survey will be conducted among the students using an adapted version of the *Physical Activity Questionnaire for Adolescents (PAQ-A)* [38] to generate self-reported data on the level of physical activity among young people. The PAQ-A is a self-administered, 7-day recall instrument. It was developed to assess general levels of physical activity for high school students approximately 13 to 19 years of age. It assesses the frequency of participation in physical activity during spare time, physical education period, lunchtime, after school, in the evenings and on weekends. A summary of the physical activity score is generated from the mean of 8 items, and ranges from 1 to 5, with higher scores indicating more frequent participation in physical activity [38]). The physical activity levels will be categorised into three; low physical activity level will be those who score between 1 to 1.9 while moderate and high physical activity levels will be those who score between 2 to 3.9 and 4 to 5 respectively [13]. For some statistical analyses, the self-reported physical activity level will be treated as a continuous variable. In a study to establish the convergent validity of the PAQ-A, the instrument was found to be significantly correlated to all self-report measures (including activity rating, *r* = 0.73; Leisure Time Exercise Questionnaire, *r* = 0.57; and 7-day physical activity recall interview, *r* = 0.59) [39]. The survey will also assess the frequency of engagement in structured physical activity from two time points (baseline and follow up) as the primary outcome measure. Based on the theory of Planned Behaviours which is the theoretical framework guiding this intervention, other variables which will be incorporated into the Physical Activity Questionnaire for Adolescents (PAQ-A) are the measures for attitude, subjective norms, perceived behavioural control and self-efficacy. A research tool which was theoretically derived by Motl et al., 2000 based on Theory of Reasoned Action (TRA) and Planned Behaviour (TPB) and Social-Cognitive Theory (SCT) will be used to assess the social-cognitive factors among this young people. This questionnaire has been tested and evidence provided for its factorial validity as a unidimensional measure of attitudes, subjective norms, perceived behavioural control and self-efficacy about physical activity among adolescent girls [40]. The core variables i.e. *knowledge of health benefits of physical activity, attitude, subjective norms, perceived behavioural control and self-efficacy about physical activity* will be analysed by scoring and summing up all question items and cut-offs will be determined using percentiles.The survey will be complemented with focus group discussions to assess their opinions about the individual, social, community, institutional and policy factors which influences the physical activity behaviours of young people.(v)Anthropometric and other physical measurements (body-mass-index for age, waist-to-hip ratio, blood pressure) will be documented. Anthropometric measurements will be taken twice and averaged; for discrepancy >10%, a third measurement will be taken. The height and weight will be assessed using standard anthropometric procedures. Height will be measured using a portable height meter/stadiometer. Students will be asked to take off their shoes and stand with their back to the portable height meter/stadiometer. The sliding bar will be lowered and pressed flat on the head and recorded to the nearest centimeter. Body weight will be measured using a digital scale and weight will be recorded to the nearest gram. Age -and sex -specific prevalence of overweight and obesity will be determined by the body-mass- index for age Z scores using the criteria defined by the World Health Organisation (WHO). According to the WHO cut off points; overweight is considered to be > + 1SD (equivalent to BMI 25 kg/m2 at 19 years), Obesity: > + 2SD (equivalent to BMI 30 kg/m2 at 19 years), Thinness: <-2SD, Severe thinness: < −3SD and Normal: > −1 to < +1 SD. Standard deviations (Z-scores) will be computed using the World Health Organisation (WHO) reference population, 2007 soft ware (Anthropometric Software Program, Version 1.0.4 [41]. Blood pressure will be measured and the mean of three measurements will be recorded. Referrals will be initiated for children whose blood pressure exceeds the 95th percentile for age. Waist circumference will be measured to the nearest 0.1 cm horizontally at the narrowest point between the lower end of the rib cage and iliac crest. Hip circumference will be measured to the nearest 0.1 cm, at the greatest horizontal circumference below the iliac crest at the level of greater trochanter. Waist hip ratio will be obtained as waist circumference/hip circumference.The fitness level of the adolescents will be measured using the 20-m shuttle run test (20-mSRT) also known as the multi-stage fitness test. The 20-mSRT is the most widely used field-based test for aerobic fitness in young people and UK percentile data and health-related cut points are available [42]. A systematic review recently concluded that the 20-mSRT is the most reliable and valid field based method to estimate aerobic fitness in young people [43]. Performance in the 20-mSRT is typically expressed as laps, levels or distance completed. The 20mSRT estimates the cardiorespiratory fitness (aerobic capacity). Children run back and forth between two lines 20-m apart following beep signals played from a pre-recorded CD. The pace of the test is ramped such that running speed increases by 0.5 km/h each minute or period. The test is finished when the child stops owing to fatigue or when he/she does not reach the line in time with the audio signal on two consecutive occasions [44]. The last completed run indicates the final result of the test. The physical fitness data will be analysed and used as continuous variables and an increase in test results will indicate higher physical fitness [45].(vi) Step count will be recorded using a pedometer. During the data collection process, 100 students (10% of the sample) will be asked to wear a Yamax SW200 Step Digi-Walker pedometer on their right hand for seven consecutive days, except during sleep and water based activities. Text messages/phone calls will be made daily as reminders to ensure compliance. The pedometers will be sealed with a sticker or cable to prevent reactivity i.e. a situation where individual change their normal activity pattern as a result of being monitored.The pedometers will be worn daily for seven days with a minimum of 4 valid days. Step counts of less than 1000 steps per day and greater than 30,000 steps per day will be treated as missing data [46]. Step count of 10,000 to 11,700 and over will be recorded as achieving the daily recommended levels of 60 min of MVPA in adolescents [47].

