### Primary outcome measurements

The primary outcome measures will be documented at baseline and final evaluation/follow-up. This include(i)Self-reported physical activity levels among the students using the International Physical Activity Questionnaire for Adolescents(ii)Step count recorded using a pedometer

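### The self-report primary outcome is not fixed: instrument name, variable, scale and time point differ between sections, and the proportion that was sized is in no outcome list

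*Protocol article*

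**What the plan says.** All references are to the protocol article.

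- **Instrument.** Primary outcome measurements lists "Self-reported physical activity levels among the students using the International Physical Activity Questionnaire for Adolescents". Data collection (iv), Table 2 and the abbreviations use the PAQ-A. The only scoring given is the PAQ-A mean score from 1 to 5, cut into low (1–1.9), moderate (2–3.9) and high (4–5).
- **Variable.** Data collection (iv) says the survey will also record "frequency of engagement in structured physical activity from two time points (baseline and follow up) as the primary outcome measure". That variable is absent from Primary outcome measurements, from the two primaries in the analysis section, and from Tables 2 and 4.
- **Scale.** The analysis section describes "self-reported physical activity level which can be a continuos or ordered categorical variable", and Table 4 lists both types. Data collection (iv) keeps the continuous form for some analyses without saying which.
- **Time point.** Primary outcome measurements says "The primary outcome measures will be documented at baseline and final evaluation/follow-up". Tables 1 and 2 schedule T0, T1 (end of intervention) and T2 (three months later). The sample size section refers to "the proportion of the participants in the exposed (experimental) group who are expected to become physically active 12 weeks after the intervention".
- **Sized endpoint.** The calculation starts from "P_1_ = 62% i.e. the proportion of the participants in the unexposed (control) group who are either moderately or vigorously physically active" and sets P2 at 72%.
- **Step count.** It is named as a primary throughout, but "100 students (10% of the sample) will be asked to wear a Yamax SW200 Step Digi-Walker pedometer".
- **Error level.** Sizing uses "Z_α/2_ = 1.96 at 5% level of error". The analysis section sets one 5% level and gives no order or split between the primaries.

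**The concern.** A primary outcome needs one instrument, one variable, one scale and one time point, fixed before the data are seen. Here the sections disagree, so a favourable score, shift in categories, proportion or structured-activity frequency, at T1 or T2, could each be defended from the text as the primary result. That allows selection after the fact. It also separates the confirmatory claim from the sample size, because the quantity that was sized is not named as an outcome. An analysis plan could not repair this without overriding one section of the protocol.

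**Working it through.** **1. Is the sized endpoint a proportion?** Inputs from the sample size section: P1 = 0.62, P2 = 0.72, z-values 1.96 and 0.84.

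n = (1.96 + 0.84)² × [0.62 × 0.38 + 0.72 × 0.28] / 0.10² = 7.84 × 0.4372 / 0.01 = 342.8, so 343 per group.

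The stated 336 is within about 2% of this (346 with pooled variance). It is a two-proportion calculation without the design effect that the section's own formula contains; that omission is a separate matter. Neither a mean score nor a step count was sized.

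**2. Can the sized proportion be found among the outcomes?** P1 adds 58.8% moderate and 3.2% high. Merging the moderate and high PAQ-A levels (score 2 or more) gives the same kind of variable. It is derivable from a listed primary, but no outcome list or analysis statement names it.

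**3. Which time point?** Read literally, 12 weeks after the intervention is close to T2. If the end of a 12-week intervention was meant, it is T1. Primary outcome measurements and Data collection (iv) speak of one follow-up, the tables of two. None says which is primary.

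**4. Error rate if any one success is enough.** For k tests each at 5%, the independent-test value is 1 − 0.95^k. It is an upper bound for correlated two-sided normal tests.

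| Tests | Independent | Common correlation 0.5 | Common correlation 0.9 |
|---|---|---|---|
| 2 (two primaries, one time point) | 9.75% | 9.1% | 7.0% |
| 4 (two primaries, T1 and T2 separately) | 18.5% | 15.6% | 9.4% |

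The correlations are assumptions; the document gives none. If both primaries must succeed, the error rate does not exceed 5%.

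**5. What can step count detect?** Assume the 100 wearers split 50 per arm and spread evenly over 11 schools per arm (100/22 = 4.55 per school). Without baseline adjustment:

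Design effect = 1 + (4.55 − 1) × ICC; detectable difference = 2.8 × √(2 × design effect / 50) SD.

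| ICC | Design effect | Detectable difference |
|---|---|---|
| 0.05 (assumed) | 1.18 | 0.61 SD |
| 0.10 (assumed) | 1.35 | 0.65 SD |
| 0.38 (the protocol's value) | 2.35 | 0.86 SD |

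Adjusting for baseline multiplies these by √(1 − r²). An assumed r = 0.5 gives 0.53–0.74 SD, and r = 0.7 gives 0.43–0.61 SD. Losses to the rule requiring four valid days would raise all of them.

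**The case against.** Much of this can be read more kindly, and several points stand.

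- **One stray label.** Only Primary outcome measurements says International; every scoring rule is for the PAQ-A. This is an erratum and gives an analyst little real freedom. That is right, but the error sits in the section that defines the primary.
- **Step count is not a conflicting definition.** A reader might infer that it is one more incompatible version of the primary. It is not: the abstract, Primary outcome measurements, the analysis section and Table 4 all name it.
- **The sized proportion is not foreign to the outcomes.** A reader might infer that no outcome relates to it. Step 2 shows that it comes from the listed PAQ-A levels.
- **Multiplicity may be settled elsewhere.** The rule can sit in an analysis plan that is not shown, and its absence alone is no fault. The planned repeated-measures mixed models may also use one group-by-time test per outcome, so separate tests at T1 and T2 are an assumption. Higher error rates, from counting the score and its own categories as extra tests, need a correlation that the document does not give.
- **Low power does not disqualify a primary.** A reader might infer that 100 pedometer wearers cannot support one. A small sample makes a true effect easy to miss, but does not by itself invalidate a positive result. Step count is also the only objectively measured primary, in a trial whose control arm receives nothing.

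None of this settles which variable, scale or time point is primary.

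**Conclusion.** The point holds for the self-report primary and should be corrected before any analysis. The contradictions are in the printed text: one misnamed instrument, one extra variable labelled primary, an open choice of scale, three descriptions of timing, and a sized proportion that is not listed as an outcome. Of these, the variable, scale and time point leave real room for selection.

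The error rates in the working are conditional. They apply only if either primary suffices, and the four-test figure also needs separate tests at T1 and T2. The step-count range of about 0.6–0.9 SD rests on an even spread of pedometers, ICC 0.05–0.38 and no baseline adjustment. It shows that this outcome was not sized, not that it must be demoted.

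**What to change.** 1. In Primary outcome measurements, replace the International questionnaire by the PAQ-A.
2. Before analysis, fix one scale and one time point for the self-report primary. Examples are the PAQ-A score at T1 adjusted for T0, or the moderate-or-high proportion that was sized. List the other versions and the other time point as secondary.
3. In Data collection (iv), remove the primary label from structured-activity frequency, or list it as secondary.
4. Reconcile the sizing section's 12 weeks after the intervention with T1 or T2.
5. Have the sample size section name the endpoint it sizes, in the words of the outcome list.
6. If step count stays a second primary, hold 5% across the two (for example by Holm), and state that it is measured in 100 students and was not sized.

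**Cost.** The changes are to wording and, where affected, the registry entry; no new data are needed. Some versions lose primary status. Holm costs some power: at its first step (2.5%, z = 2.24), an outcome sized for exactly 80% keeps Φ(2.80 − 2.24) = Φ(0.56), about 71%. Restoring 80% at that level would need 416 instead of 343 per group before any design effect. Choosing the score in place of the proportion means a new sizing calculation, and any restatement will have to deal with the design effect left out of 336.

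### The 10% bivariate screen and the baseline tests of the arms ignore school clustering, contradicting the statement that all analyses carry random effects

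*Protocol article*

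**What the plan says.** All of this is in the Protocol article, section Data management and statistical analysis.

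- **Baseline comparison.** Cross tabulation at baseline "will be used to compare the differences in proportions of the primary and secondary outcome measures of the experimental and control groups".
- **Tests named next.** Chi-square "will be used for significance testing of the self-reported physical activity levels (dependent ordered categorical variable) and other categorical independent variables". A different test is named for the pedometer outcome: "repeated measures ANOVA will be used for Step count (average steps/day").
- **Entry rule.** On the strength of those bivariate results, "all independent variables which are significant at 10% will be incorporated into the regression model".
- **Predictor regression.** "Regression analysis will be used to assess the extent to which the independent variables predict self-reported physical activity levels and step count (average steps/day").
- **Intervention effect.** A separate sentence specifies "multilevel mixed effects models for repeated measures adjusted for relevant confounding factors". The confounders are not named.
- **Clustering.** Because the data are clustered, "random effects for the cities and schools will be included in all analyses".

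Elsewhere, Blinding and sampling technique describes 22 schools pair-matched on ownership and population size. Sample size for the intervention study adopts an ICC of 0.38. Data collection limits pedometers to 100 students.

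**The concern.** An ordinary chi-square test cannot contain a random effect, and repeated-measures ANOVA as named has no school term. The testing step and the statement about all analyses therefore cannot both be followed.

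The position of repeated-measures ANOVA is also unclear. Read as a baseline test, it has only one average steps-per-day value per student, so nothing is repeated. Read as covering the three time points, it competes with the mixed model described shortly afterwards.

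Two things are at stake. First, identifying school environment and policy influences is a stated objective. Those scores are fixed within a school, which is where an unclustered test does worst, so null school factors would often pass the screen. Second, a naive baseline test of the arms has the same fault and would often label chance differences between a few schools as significant imbalance.

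**Working it through.** The protocol gives no error rate for its screen, so there is no figure of its own to reproduce. The check asks what the true size of the named tests is under the protocol's own clustering assumptions.

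**Inputs**
- Outcome ICC: 0.38 (Sample size for the intervention study).
- Students per school: 1000/22 = 45.45. The sample-size text uses 50.
- Nominal levels: 10% for entry (z = 1.645) and 5% (z = 1.96).
- Pedometer subset: 100 students, or 100/22 = 4.55 per school if evenly spread (assumption).
- Between-school ICC of each covariate: not given, so a range is shown (assumption).

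**Formulas**
- Design effect D = 1 + (m − 1) × ICC of covariate × ICC of outcome. A school-level factor, or arm, has covariate ICC 1.
- True size of a naive test = 2 × [1 − Φ(z/√D)].

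**School-level factor or arm, self-reported activity**
- D = 1 + 44.45 × 0.38 = 17.89, √D = 4.23.
- Nominal 5%: 1.96/4.23 = 0.463, true size 0.643.
- Nominal 10%: 1.645/4.23 = 0.389, true size 0.697.
- With 50 per school, D = 1 + 49 × 0.38 = 19.62 and the nominal 10% size is 0.71.
- With outcome ICC 0.05 (assumed), D = 3.22 and the sizes are 0.275 at 5% and 0.36 at 10%.

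**Other covariates, outcome ICC 0.38, nominal 10%**

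| Covariate ICC (assumed) | D | True size, formula | True size, simulated |
|---|---|---|---|
| 1 (school-level) | 17.89 | 0.697 | 0.715 |
| 0.38 | 7.42 | 0.546 | 0.535 |
| 0.10 | 2.69 | 0.316 | 0.305 |
| 0.05 | 1.84 | 0.226 | 0.218 |
| 0 | 1.00 | 0.100 | 0.091 |

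The simulation applied a chi-square test to beta-binomial data (22 schools of 45 students, 62% active, 3000 replicates). With outcome ICC 0.05 and a school-level factor it gave 0.354, against 0.36 from the formula.

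**Step count, school-level factor**
- D = 1 + 3.55 × 0.38 = 2.35, √D = 1.53.
- Nominal 10%: 1.645/1.53 = 1.07, true size 0.28. Nominal 5%: about 0.20.
- The ICC of 0.38 comes from self-reported activity, so using it for step count is a further assumption.

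**Limits.** The calculation treats each test as a two-group comparison of a binary or continuous outcome; the three-category chi-square was not computed. The figures for arm take no credit for pair matching, which would lower them to the extent that ownership and school size explain between-school variation.

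**The case against.** The strongest reply is that the screen belongs to the predictor regression, which is the sentence that follows it, and that the intervention effect has its own clustered model. That stands, and it rules out several stronger readings that a reader might infer.

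- **That the adjusted intervention effect depends on which p-values fall below 0.10.** The text never says that the screened variables are the ones meant by "adjusted for relevant confounding factors". The link is plausible, because the 10% rule is the only selection rule given, but it is not stated. Nor is the missing covariate list a finding in itself, since a condensed article may leave it to a fuller document.
- **That the baseline outcome is adjusted for only if it passes the screen.** Activity and step count are the dependent variables and are measured at T0, T1 and T2. A repeated-measures model can take T0 as one of its time points.
- **That 70% of null school factors would be declared predictors.** The screen only admits variables. Significance is then judged at 5% in a regression that is meant to carry school effects, so an entry rate is not a false-declaration rate. A liberal screen would also tend to retain ownership and school size rather than lose them.
- **That every variable is inflated to this degree.** Knowledge, attitude, self-efficacy and sex vary within schools, and the table shows how quickly the excess shrinks.

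The clustering sentence might also be meant only for the regression and mixed models. The wording would then no longer conflict, but the screening and baseline tests would remain unclustered, so the defect stays.

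**Conclusion.** The point holds for the screening step and the baseline comparison of the arms. As written, both use tests without a school effect, against the protocol's statement about all analyses.

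The consequence is large where it applies. For a purely school-level factor or an arm comparison on self-reported activity, true size is about 64% at nominal 5% and 70% at nominal 10%, given ICC 0.38 and 45 students per school. It is about 36% at nominal 10% if the ICC is 0.05. For student-level covariates it runs down to the nominal 10% as their between-school variation vanishes. For step count it is about 28% at nominal 10%, given an even spread of the 100 students and the same ICC.

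The intervention-effect model is itself described as clustered, and no error in it is shown. What needs settling there is whether the 10% screen chooses its covariates.

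**What to change.** 1. For the predictor objective, replace chi-square and repeated-measures ANOVA with mixed or cluster-robust models in every bivariate test.
2. Report baseline characteristics by arm descriptively, without p-values.
3. State that the 10% screen does not govern the intervention-effect model. Give that model a fixed set: school ownership, school population size, sex and age. Let T0 enter either as a modelled time point or as a covariate, not both.
4. Do not add LGA as a fixed covariate yet. In Blinding and sampling technique, Step 2 makes one LGA experimental and the other control, whereas Step 3 randomises matched schools. Under Step 2, LGA would coincide with arm and the effect could not be separated from it. Reconcile the two steps first.

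The cost is a change to the analysis wording. Ownership and school size are already used for matching, sex is used in sampling, and the questionnaire collects demographic data.
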